There are less commonly prescribed, more advanced ESR options commercially available, including articulating ankles that can present as a passive hydraulic, microprocessor-controlled, or powered units (Figure 2). Articulating ankles in prosthetic feet have been traditionally thought to decrease energy return for individuals with transtibial amputation (TTA), but recent evidence on current articulating ESR ankle-foot units (i.e. Endolite Echelon, Fillauer Motion Foot, Freedom Innovations Kinterra, Otto Bock Triton Smart Ankle, Ossur Proflex) and microprocessor controlled ESR ankle-foot units (i.e. Endolite Elan, Ossur Propriofoot, Hosmer Raize), suggest that articulating hydraulic and microprocessor-controlled non-powered ankle-foot units can improve ambulation on level ground as well as on inclines and stairs (10). De Asha et al. described improved progression of the center of pressure in a prosthetic foot with a hydraulic ankle unit in a population of individuals with TTA and transfemoral amputation (TFA) (13), and Portnoy et al. found a decreased load at heel strike when using an ESR hydraulic ankle-foot unit (14). Fradet et al. reported that a microprocessor controlled ankle improved kinematics in ramp ascent and made patients feel safer during ramp descent (15). This evidence suggests that Veterans and Service Members with TTA that negotiate specific environments may benefit from an articulating ankle ESR foot over a fixed-ankle ESR foot.

[figure not shown]

Figure 2. Articulating ankle ESR feet, clockwise from top left Propriofoot, Echelon, Kinterra,

Commercially available ESR feet with active (i.e. powered) plantarflexion (i.e. iWalk BiOM) have potential biomechanical benefits to the user beyond that of the ESR or articulating ankle ESR options (Figure 3). The iWalk BiOM (Bedford, MA) works to replicate the dynamic contractile tissues of the gastroc-soleus complex for individuals with a lower extremity amputation (16). This biomimetic prosthetic device has the ability to normalize ankle power, potentially reducing kinetic asymmetries that lead to musculoskeletal

imbalances, thus improving physical function (16). Grabowski and D'Andrea noted that individuals with TTA using the BiOM had a reduction in peak resultant force and knee adduction moment on the unaffected leg during level-ground walking, potentially limiting the risk of secondary musculoskeletal comorbidities which are common in this population (11, 17-20).

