### **Foot Selection:**

Prosthetic ankle-foot units included in this study will be grouped in to three categories: 1) Non-articulating ESR - this group will be any qualifying ESR ankle-foot unit that is commercially available. This will typically be the foot the subject is currently using. This group contains over 100 commercially available prosthetic feet, and will be randomly chosen from all available options that fit the subject’s anatomy if the user does not current have a non-articulating ESR foot. 2) Articulating ESR – this group includes all commercially available options

that have an articulating ankle and also have ESR qualities, currently Endolite Echelon, Fillauer Motion Foot, Freedom Innovations Kinterra, Endolite Elan, Ossur Propriofoot, Hosmer Raize, Otto Bock Triton Smart Ankle, and Ossur Proflex (Figure 2) meet this criteria. 3) Active (Powered) Plantarflexion - the third group will contain all commercially available ESR ankle-foot units with active plantarflexion. Currently, the iWalk BiOM is the only foot that would be classified into the Active Plantarflexion ESR group. If new prosthetic feet-ankle units become commercially available during the course of this study, they will be added to the appropriate groups.

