*Articulating ESR Group:* The articulating ESR group contains mechanical and microprocessor controlled prosthetic ankle-foot units. While there is research comparing these devices to SACH feet and non-articulating ESR feet, there is no current research suggesting any differences between the feet within this group in their effect on functional performance. These prosthetic ankle-foot units have articulation ranges from 9 to 50 degrees within this group, and it has been reported that average range of motion in a healthy individual with an intact lower limb is 20-40 degrees for ankle plantar/dorsiflexion (25). There is no published research to-date as to the ideal range of motion for an individual with transtibial limb loss, so all ankle-foot units will be included. Internal analysis within all groups will be conducted at the completion of this study to substantiate or rebut these groupings, and to determine if there are in fact outliers that should be classified differently clinically or in future research.

*Active Plantarflexion ESR Group:* Criteria for this group includes the following

- Commercially available
- Must be articulating
- Provides plantarflexion energy during terminal stance at a rate that is greater than the total energy absorbed (i.e. >100%)

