### **Specific Aim 1:** Assessment of function using ESR, Articulating ESR and Active Plantarflexion ESR ankle-foot prostheses

Parts 2-4 of the study will address Specific Aim 1. Part 2 will begin with issuing the first of the 3 well-fitting prostheses according to the randomization schedule, including a 1 week acclimation period. At the conclusion of this acclimation period, a battery of outcome measures and surveys (outlined below) will be collected. For Part 3, the subject will receive the second prosthesis according to the established randomization schedule and the initial prosthesis will be returned to the study prosthetist. The subject will again have a one week acclimation period followed by the collection of the same battery of outcome measures and surveys. The third prosthesis will be issued during part 4, and the second prosthesis will be returned to the study prosthetist. The subject will receive the same one week acclimation followed by the battery of outcome measures and surveys.

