The PEQ contains a VAS for pain within the evaluation. Spearman correlations, a statistical measure of the strength of a monotonic relationship between paired data will be calculated to correlate data between pain and functional outcome values across the 3 groups. Linear mixed-effects models will be used to identify statistically significant differences in pain scores and functional outcome variables. In the case of significance, pair-wise comparisons will be tested for significance using linear contrasts with Tukey's Honestly Significant Difference or applying Bonferroni's correction. Finally, stepwise multiple regression will be performed with VAS pain as the dependent variable. The independent variables will be comprised of functional parameters and condition (foot type). Significance will be set at  $p < 0.05$ . Variables will be eliminated if  $p$  is  $> 0.1$ .

*Hypothesis 1.4 There will be no significant differences in functional outcome measures within all tested non-articulating ESR feet regardless of specific foot assigned.*

*Hypothesis 1.5 There will be no significant differences in functional outcomes within all articulating ESR feet tested regardless of specific foot assigned.*

Functional measures will be analyzed by multilevel (site) repeated measures analysis of variance. Because order of prosthesis will be randomized, there should be no order effect. However, order will be included in the initial analysis to test this assumption. When the ANOVA reveals significant differences ( $p < 0.05$ ), we will apply pairwise comparisons using related pairs t-tests to identify the source of differences ( $p < 0.05$ ).

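### The post-hoc step for Hypotheses 1.4 and 1.5 cannot compare individual feet as written, and run between subjects without adjustment it would give false differences in about 20-43% of trials per outcome

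*Protocol*

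**What the plan says.** Hypothesis 1.5 in the Protocol, section SAI: Data and Statistical Analysis, reads "There will be no significant differences in functional outcomes within all articulating ESR feet tested regardless of specific foot assigned"; Hypothesis 1.4 says the same of non-articulating feet. One paragraph of analysis serves both. It gives a repeated-measures ANOVA with site as a level and order tested first. If p < 0.05, "we will apply pairwise comparisons using related pairs t-tests to identify the source of differences", again at p < 0.05. No adjustment is named.

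Under Hypothesis 1.3, in the same section, "pair-wise comparisons will be tested for significance using linear contrasts with" Tukey's HSD, or a Bonferroni correction is applied. SA2 Statistical Analysis has the same rule.

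Foot Selection lists the articulating feet: "currently Endolite Echelon, Fillauer Motion Foot, Freedom Innovations Kinterra, Endolite Elan, Ossur Propriofoot, Hosmer Raize, Otto Bock Triton Smart Ankle, and Ossur Proflex". If further devices reach the market, "they will be added to the appropriate groups".

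The Specific Aim 1 description starts: "Part 2 will begin with issuing the first of the 3 well-fitting prostheses according to the randomization schedule". With three prostheses and three categories, this implies one foot per category for each subject.

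The Justification section says that an internal analysis within all groups will "determine if there are in fact outliers that should be classified differently clinically or in future research".

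**The concern.** There are two faults in the same step.

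First, the test does not match the question. A related-pairs t-test needs both feet measured in the same subject. No subject is planned to wear two articulating feet, so none of the within-category pairs can be tested this way.

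Second, the natural repair is to run the same unadjusted tests between subjects, and that leaves the error rate uncontrolled. An overall test at 0.05 followed by unadjusted pairs holds the familywise error when there are three groups. With eight, it does so only if all eight are alike. Once one foot differs, that foot makes the overall test significant and the pairs among the other seven are each tested at the full 0.05.

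The case that goes unprotected is the one the outlier check is meant to find. At stake is whether a foot is reported as out of line with its category, in a study meant to inform prescription guidance. The protocol already corrects its pairs in two other places where fewer pairs are at issue.

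**Working it through.** **Inputs from the protocol.** Eight articulating feet (Foot Selection). N = 120, alpha 5%, SD 5, difference 3 units, so 3/5 = 0.6 SD (Power Analysis, Specific Aim 1).

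**Assumptions.** Even allocation, 120/8 = 15 subjects per foot; normal data with equal SD; two-sided tests; between-subject comparisons with pooled variance; exactly one foot shifted and seven identical.

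**The plan's own figure.** Three conditions with means -1.5, 0, +1.5 and SD 5 give λ = 120 × (1.5² + 0² + 1.5²)/25 = 21.6. The power of F(2, 357) is then 99.0%, consistent with the stated figure of over 98%. It concerns differences between the three categories. The protocol gives no error rate or power for feet within a category.

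**Pairs.** 8 × 7/2 = 28 in all. Among the seven identical feet, 7 × 6/2 = 21.

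**Limit when the outlier is obvious.** The overall test is then always significant. The chance that at least one of the 21 null pairs reaches p < 0.05 is the chance that the studentized range of 7 means exceeds √2 × t(0.975; 112) = 1.414 × 1.981 = 2.80. With 112 df this is 43.2% (44.1% with infinite df).

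**With the ANOVA gate.** For an outlier of d SD, λ = 15 × d² × 7/8. At d = 0.6 this is 4.725, and F(7, 112) is significant with probability 28%. Simulated one-way layouts (400,000 per setting) give, per outcome:

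| Outlier (SD) | ANOVA significant | False pair among the 7, all trials | False pair, given significant ANOVA | All trials, Tukey over 28 pairs |
|---|---|---|---|---|
| 0 (all alike) | 5% | 5% | – | 3% |
| 0.6 | 28% | 20% | 72% | 4% |
| 0.8 | 50% | 30% | 60% | 4% |
| 1.0 | 72% | 38% | 52% | 4% |
| 1.2 | 89% | 42% | 47% | 4% |
| 1.6 | 99% | 43% | 43% | 4% |

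In the first row all eight feet are alike, but the count is still over pairs among seven of them. The third and fourth columns are linked: at 0.6 SD, 0.20/0.28 ≈ 0.72. Bonferroni at 0.05/28 gives about 3% when one foot differs.

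**Sensitivity.** With 12 per foot, the all-trials rate runs from 17% at 0.6 SD to 43% for a clear outlier. One uneven allocation (5 to 30 per foot) gives 29-43%.

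**Cost of correcting.** For one pair at 3 units, SD 5, 15 per foot, the noncentrality is 0.6 × √(15/2) = 1.643. By normal approximation, power at 0.05 is Φ(1.643 - 1.960) ≈ 38%. At 0.05/28 it is Φ(1.643 - 3.124) ≈ 7%.

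**The case against.** The strongest counter-argument is that the 28-pair reading is not forced. The post-hoc sentence is the one used for Hypothesis 1.2, where it compares the three testing conditions. The ANOVA text is repeated in the Power Analysis for differences between ESR groups. Repeated measures, order effects and related pairs all fit a three-category comparison, which has three pairs protected by the overall test. This stands as a reading of the wording, but it does not rescue the plan: on that reading Hypotheses 1.4 and 1.5 have no analysis at all.

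The between-subject tests used in the working are also not what the protocol states. That is correct. A reader might infer that the plan as written will often declare identical feet different. It will not, because the written test cannot be run on these pairs. The error rates describe the nearest workable version without adjustment.

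A reader might also take a rate such as 44-61% as the chance of a false difference whenever one foot differs. Rates of that size at moderate shifts hold only given a significant ANOVA. Over all trials the rate is at most about 43-44%, about 20% at the protocol's own 0.6 SD, and 5% if all feet are alike.

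The outlier check is described as an internal analysis and does not cite these t-tests. It also looks toward future research as well as clinical classification. So the tests can misclassify feet; the documents do not say that a pairwise p-value alone decides.

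Finally, one might argue that the plan must test mechanical against microprocessor control or articulation range. The protocol mentions these traits while justifying a single pooled group, and Hypothesis 1.5 asks about the specific foot. A foot factor answers that question, so trait contrasts are a preference.

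**Conclusion.** The point holds in this form. The stated post-hoc step for Hypotheses 1.4 and 1.5 does not fit hypotheses about individual feet, and its unadjusted 0.05 threshold would not control error if the tests were moved between subjects. With one articulating foot off by 0.6 to 1.6 SD, a false difference among the other seven is expected in about 20-43% of trials per outcome. Among trials with a significant ANOVA the figure is about 43-72%. Tukey holds the all-trials rate near 4%.

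This rests on the within-category reading, one articulating foot per subject (implied by the design), and the allocation and distribution assumptions listed. Weight, height and activity limits on device choice may make allocation uneven.

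No size is claimed for the non-articulating group. Over 100 feet are eligible, but how many will be tested is unknown, since subjects will typically keep their current foot. Hypothesis 2.5 is not part of this point, because Aim 2 already names a correction.

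**What to change.** For Hypotheses 1.4 and 1.5:

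- Replace the related-pairs t-tests with a between-subject comparison of specific feet within each category, with foot as a factor in the multilevel model.
- Adjust over all pairs of feet tested in the category, by Tukey-Kramer (which allows unequal numbers per foot) or Bonferroni/Holm, in line with what Hypothesis 1.3 and Aim 2 already name.
- State that a foot is called an outlier only on the corrected result.
- State that a non-significant pair does not show equivalence.

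The change is to wording only; subjects, visits and data stay the same. The price is sensitivity: for a 3-unit difference at SD 5 and 15 per foot, single-pair power falls from about 38% to about 7% under Bonferroni over 28 pairs. Because both hypotheses predict no difference, that loss makes the last item essential.

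A single contrast of mechanical against microprocessor feet may be added, but it is optional.

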## **Specific Aim 2:**

Specific Aim 2 will be addressed through a subset of  $n=30$  subjects which will undergo kinematic and kinetic biomechanical evaluations at the completion of each acclimation period for Parts 2-4. This will include kinetic and kinematic evaluation on level ground walking, and additional kinematic evaluation on inclines and declines.

## **Gait Analysis**

**Instrumentation:** Gait analysis will be performed at the VISN 3 Gait and Motion Analysis Laboratory at VA NYHHCS and the Biomechanics Laboratory at WRNMMC. The VISN 3 Gait and Motion Analysis Laboratory is a 1,440 square foot space comprised of an eight-camera infrared motion analysis system (Vicon Inc. Oxford, UK) with 4 multi-axis force plates (2 AMTI – Waterford, MA and 2 Kistler - Winterthur, Switzerland). The system records the position of passive reflective markers at a rate of 120 Hz, and force plates sample data at a rate of 3,000 Hz. At WRNMMC, the Amputee Care Service within the Department of Rehabilitation houses the Center for Performance and Clinical Research (CPCR) which includes the Biomechanics Laboratory. The Biomechanics Laboratory is a 1,200 square foot space comprised of a 27 camera motion capture system (Vicon Inc. Oxford, UK), and 6 6-degree-of-freedom force platforms (AMTI, Waterford, MA). Visual3D software (C-Motion Inc, Rockville, MD) will be utilized for analysis of 3D motion capture data. It is hardware independent and provides clinically validated, consistent results.

**Kinematic and Kinetic Data Capture:** Gait analysis will be performed after each acclimation period completing Part 2, Part 3 and Part 4 of the study. Wearing shorts, each test subject be provided with biomechanically neutral shoes that offer neither supinatory nor pronatory control. A custom, full-body passive reflective marker set will be placed on each subject, which tracks each segment independently, allowing for the accurate

measurement of movements. A total of 60 markers will be placed or digitized on the trunk and extremities. Marker placements for the prosthetic limb will be matched to those of the intact leg. The cluster technique will be employed to minimize the surface to bone displacements for the thigh, shank, and upper arm mounted markers (39). As such, tracking clusters will be placed bilaterally on the thigh, shank (tibial crest), and upper arm. Functional joints will also be calculated for the intact ankle, knee, and hips, adapted from Schwartz and Rozumalski (40).

**Procedure:** During each experimental session, subjects will walk at 3 speeds across a 10 meter instrumented walkway until 5 trials when each foot makes full contact with each force plate for at least two sequential foot strikes. Since kinetic outcome measures are speed dependent, subjects will ambulate with controlled speeds determined by normalizing to each subject's intact limb length (41). Subjects will walk at their defined median Froude speed (FR3) and at one speed below and one speed above the median (FR2 & FR4), respectively. Auditory feedback will be provided to the subject in the form of a tone to ensure that they are walking at the correct speed. Subjects will be asked to repeat the walking trials until 5 acceptable trials for each speed are collected. The main purpose of this session is to collect joint motion data, force, torque, and power on subjects during each test condition. Segment ranges of motion, velocities and accelerations, and corresponding hip, knee, and ankle joint moments of force and generated/absorbed powers will be computed using inverse dynamics methods. Averages, maximum and minimum values, standard deviations and coefficients of variation will be computed for the values attained per gait cycle over each trial and for each set of trials. Spatial and temporal parameters, such as stride and step lengths, step times and velocities will also be recorded.

Additionally subjects in this subset will perform ramp ascent and descent under the collection of kinematic data. This will be performed on a standardize ramp of 1:6 rise:run ratio, which is steeper than ADA guidelines. Subjects will be instructed to ambulate at a comfortable self-selected walking speed. This will include 5 trials ascending and 5 trials descending.

**SA2 Data Analysis:** The reflective marker positions will be digitized using motion tracking software (Vicon, Oxford, UK). A 15-segment (head, trunk, pelvis, and bilateral upper/lower arm, hand, thigh, shank, and feet) rigid body model will be created based on the skin-mounted markers and functional joints. Local coordinate systems for each segment will be defined using the International Society of Biomechanics (ISB) recommendations (42, 43). The data of 5 acceptable walking trials of each participant at each speed will be processed using Visual3D (C-Motion Inc., Rockville, MD). Marker data will be filtered with a 6 Hz Butterworth low-pass filter. Raw analog data will be filtered using a second-order low-pass Butterworth filter with a 25 hertz cutoff frequency. Visual 3D software will be used to calculate temporal-spatial values, walking velocity, as well as lower extremity kinematics and kinetics. Inverse dynamics analysis is applied to the kinematics of the biomechanical model and to the location, magnitude, and direction of ground reaction forces acting on the foot to calculate lower extremity joint torques and powers, including ankle, knee, and hip power of the biological and prosthetic limbs over stance phase, as well as the frontal plane knee moments for the unaffected legs of all subjects. The resultant ground reaction force will be calculated as the magnitude of the ground reaction force vector.

### **SA2 Statistical Analysis:**

To address the hypotheses stated for SA2, several parameters, including temporal-spatial variables (step lengths, stance/swing times, cadence, and stride length), peak angles, moments, and powers for the ankles, knees, and hips during each phase of gait, and other biomechanical parameters (external adduction moment rate, impulse external knee adduction moment, peak vertical ground reaction force, peak resultant ground reaction force, etc.) will be measured and statistically compared across all conditions. Peak values are identified as the greatest local maxima during the first half of stance. We will use linear mixed-effects models to identify statistically significant differences in gait temporal-spatial and biomechanical variables. The fixed effects for our study will be the average differences in gait biomechanical and temporal-spatial variables by prosthetic foot type. For example, we will use a linear mixed effects regression to examine the relationship between intact knee peak EAM and prosthetic foot condition. Peak intact knee EAM will be the dependent variable, while foot condition will be the independent variable and subject by foot condition will be modeled as random effects. In the case of significance, pair-wise comparisons will be tested for significance using linear contrasts with Tukey's Honestly

Significant Difference or applying Bonferroni's correction. We will also use linear mixed effects regression to determine the association between prosthetic peak ankle power and foot condition.

### Specific Aim 3

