### Specific Aim 2– To evaluate the kinematic and kinetic differences of non-articulating ESR, articulating ESR, and active plantar flexion ESR feet in individuals with transtibial amputation

Hypothesis 2.1 Plantarflexion forces (i.e. ground reaction forces) at push off /terminal stance will be most symmetrical to the intact limb for active plantarflexion devices, followed by non-articulating ESR feet, and lastly articulating ESR devices.

Hypothesis 2.2 Biomechanical symmetry in gait while negotiating a decline will be greater for both active plantarflexion ESR and articulating ankle ESR conditions compared to non-articulating ESR feet.

Hypothesis 2.3 Biomechanical symmetry in gait while negotiating an incline will be greatest for devices with active plantarflexion, followed by articulating devices, and lastly non-articulating ESR feet.

Hypothesis 2.4 Ambulation at a faster than self-selected walking speed will yield decreased symmetry in articulating ankle ESR and non-articulating ESR feet but not with the active plantar flexion ESR feet.

Hypothesis 2.5 Articulating ESR feet will not yield significant differences in gait symmetry regardless of specific foot assigned within the articulating ESR category.

**Specific Aim 3 – To correlate biomechanical findings with functional and subjective outcome measures and with user preference determined through activity monitoring and user satisfaction to develop guidelines for appropriate prosthetic prescription.**

Hypothesis 3.1 Individuals that commonly negotiate ramps, hills, inclines or declines will show preference for an articulating ankle ESR and/or active plantarflexion ESR feet over non-articulating ESR feet

Hypothesis 3.2 Individuals that have higher step counts, but do so at a low activity level will prefer the active plantarflexion ESR ankle-foot prosthesis.

Hypothesis 3.3 The majority of subjects will chose to utilize a single prosthesis for all activities, and not use different prostheses for different activities, as measured through step activity monitoring and daily activity logs.

Hypothesis 3.4 Step activity performance will, and age will not, correlate with prosthetic feet category that best optimizes function.

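### The first-half-of-stance rule for peak values excludes push-off: applied literally it cannot test Hypothesis 2.1, and for joint powers it contradicts the sentence before it

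*Protocol*

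**What the plan says.** SA2 Statistical Analysis lists the variables that will serve the Aim 2 hypotheses. One group is joint-level: "peak angles, moments, and powers for the ankles, knees, and hips during each phase of gait". A second group holds other biomechanical parameters and ends with "peak vertical ground reaction force, peak resultant ground reaction force, etc.) will be measured and statistically compared across all conditions". The next sentence sets the peak rule: "Peak values are identified as the greatest local maxima during the first half of stance". The worked example after it is the peak external adduction moment of the intact knee. The section closes with a second named model: "We will also use linear mixed effects regression to determine the association between prosthetic peak ankle power and foot condition".

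Hypothesis 2.1, under Specific Aim 2, reads: "Plantarflexion forces (i.e. ground reaction forces) at push off /terminal stance will be most symmetrical to the intact limb for active plantarflexion devices", with the non-articulating feet ranked next and the articulating feet last.

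Under the justification for including all commercially available feet, one criterion for the active plantarflexion category is: "Provides plantarflexion energy during terminal stance at a rate that is greater than the total energy absorbed".

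On data reduction, the gait Procedure text computes maxima and minima per gait cycle. The SA2 Data Analysis text computes joint powers, "including ankle, knee, and hip power of the biological and prosthetic limbs over stance phase".

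**The concern.** The peak rule decides which number leaves the gait software and enters the mixed models. It fixes one window, early stance, straight after a list that includes the ground reaction force peaks and the joint powers. Push-off is outside that window.

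If a programmer follows the sentence, Hypothesis 2.1 is tested on a loading-phase force. A finding of no difference between foot categories would then say nothing about push-off, yet it could be read as evidence against the powered foot. Prosthetic peak ankle power would likewise omit the phase in which the protocol says the active category delivers its energy. Biomechanical parameters are also one of the domains in the prescription model (Development of Prediction Model), so a wrongly windowed peak could carry over into Aim 3.

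If the programmer does not follow the sentence, the window is chosen outside the protocol, possibly after data have been seen.

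**Working it through.** No sample size, power or alpha figure in the protocol bears on this point, so there is no stated figure to reproduce. The check sets the statements side by side.

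| Quantity | Phase in which it is wanted | Source | Covered by a first-half window? |
|---|---|---|---|
| Ground reaction force symmetry (Hypothesis 2.1) | Push-off / terminal stance | Specific Aim 2 | No |
| Energy delivery that defines the active category | Terminal stance | Foot category criteria | No |
| Prosthetic peak ankle power | Not stated for this model; joint powers are listed for every phase | SA2 Statistical Analysis | Only in part |
| Intact-knee adduction moment, first peak | Loading | Worked example, SA2 Statistical Analysis | Yes |

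**Step 1, forces.** The phrase about every phase of gait qualifies joint angles, moments and powers. The vertical and resultant force peaks stand in the separate list of other parameters, so that phrase does not reach them. The protocol defines no push-off force peak for comparison. For these variables the first-half rule is the only stated window, and it misses the phase that Hypothesis 2.1 names.

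**Step 2, joint powers.** Here two adjacent sentences give incompatible instructions. Every phase of gait includes terminal stance and swing; the first half of stance includes neither.

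**Step 3, does a first-half maximum carry any push-off information?** As an illustration, take an assumed two-hump stance curve with *t* as the fraction of stance:

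g(t) = 1.10·exp(−((t − 0.25)/0.15)²) + L·exp(−((t − 0.75)/0.15)²)

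The early hump is fixed at 1.10 and only the late (push-off) hump L varies.

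| L | Maximum, first half | Maximum, second half |
|---|---|---|
| 0.80 | 1.10 | 0.80 |
| 1.05 | 1.10 | 1.05 |
| 1.30 | 1.10 | 1.30 |

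Put as symmetry, suppose the intact limb has L = 1.30 and the prosthetic limb L = 0.80. The late-peak ratio is 0.80/1.30 = 0.62. The first-half ratio is 1.10/1.10 = 1.00, so the rule would report perfect symmetry. The amplitudes are invented and show the mechanism only; they do not predict an effect size.

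**Step 4, are the data there?** Yes. Joint powers are computed over stance for both limbs, and maxima and minima are taken per gait cycle. A whole-cycle force maximum does not isolate push-off, since it may be the loading peak, but the recorded curves contain the late peak.

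**The case against.** The best defence is that the sentence was never meant to be global. It follows the knee adduction and force variables and precedes an intact-knee example. The Background cites a study of a powered foot that reported lower peak resultant force and knee adduction moment on the unaffected leg. Those are loading measures, for which an early window is proper. A global rule would also remove every swing-phase peak and empty the neighbouring phrase of meaning. Hypothesis 2.1 names its own phase and its own comparison with the intact limb, and the parameter list is open-ended.

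Much of this stands as an account of intent, and for ankle power it gives a sensible reading. It does not repair the text. The sentence names no variable, the force peaks are among those it directly follows, and no late-stance force peak is defined elsewhere. Window details may commonly be left to a SAP, but here the protocol has already fixed a window. A SAP would have to inherit the error or depart from the protocol.

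A reader might infer more: that the Hypothesis 2.1 endpoint and the ankle power analysis are lost entirely, at every speed and in every condition, with no power left. The documents do not support that. The push-off data are captured and can be reprocessed. For ankle power there is a contradiction, not a certain loss. Ramp trials are kinematic only, so no ramp force or ankle power exists to lose. Nor is it shown that Hypotheses 2.2 and 2.3 depend on a push-off force or ankle power peak.

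**Conclusion.** The peak rule is wrong as written. For ground reaction force it yields a loading-phase value where Hypothesis 2.1 needs a push-off value. For joint powers, including prosthetic peak ankle power, it conflicts with the sentence before it and, read literally, omits the phase that defines the active category.

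The extent is one hypothesis clearly and one named model arguably, in the level-ground trials of the 30-subject gait subset (15 at each of two sites). Recruitment, data capture, randomisation and the Aim 1 analyses are untouched. No numerical loss of power can be derived from the documents.

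The conclusion rests on two assumptions: that push-off and terminal stance lie in the second half of stance, which is the usual division although the protocol gives no percentages; and that the sentence is applied to the variables it follows.

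**What to change.** Replace the single sentence with a scoped rule:

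- Keep the first-half-of-stance window for loading-phase variables only: the first knee adduction moment peak and the first vertical or resultant ground reaction force peak.
- State that the Hypothesis 2.1 force peak, prosthetic ankle power generation and the ankle plantarflexion moment are taken in the second half of stance (terminal stance).
- State that Hypothesis 2.1 is analysed as prosthetic-versus-intact symmetry of that terminal-stance force peak, compared across the three foot categories.

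This also removes the conflict with the wording on phases of gait. The cost is a short protocol edit and a change to the processing script. No new data, visits or subjects are needed. The edit should be made before peaks are extracted for any analysis, so that the windows are not chosen after results are known.
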